### Hypotheses

We hypothesized that, compared to the waiting list control group, both MBHC and MBHC-VR will improve occupational indicators (Hypothesis 1), mental health (Hypothesis 2), and psychological functioning (Hypothesis 3). We expect that, compared to MBHC, MBHC-VR will have higher adherence to home practice [5], and result in greater magnitude of change in the occupational balance, mental health and psychological functioning variables (Hypothesis 4). Furthermore, we expect that improvements will be maintained at 3-months post-intervention completion [5] (Hypothesis 5). Finally, we predict that psychological functioning variables will act as mechanisms of change of occupational balance and mental health indicators in experimental vs control condition [35] (Hypothesis 6). All hypotheses will be tested in the post-training assessment, except for hypothesis 5, which will be tested in the follow-up.

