### Sample size estimation

G *Power (v. 3.1) was used to estimate the sample size needed to test hypotheses 1, 2, 3 and 5. A mixed model using treatment as a between-subjects factor (MBHC, MBHC-VR, and WL) and time as a within-subjects factor (pre, inter, post, and follow-up) will be tested. Interaction effect was powered. The sample size was estimated taking as a reference a small difference in perceived stress between MBHC with vs without VR-assisted meditation in university students [5]. With an alpha criterion of .05 and a small effect size (Cohen’s d^2^ = .08), to achieve a minimum of 80% power, a minimum sample size of 174 participants will be needed. Assuming an attrition rate, based on complete dropout of approximately 20% [5], the final sample needed will include at least 210 university students (i.e., 70 participants in each of three groups).

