### Data analysis

#### Quantitative data analysis plan

The data analysis plan will be conducted following four steps. R Software [66] will be used for all data cleaning and statistical tests with a significance level of alpha < .05.

*Data preprocessing*. Demographics and clinical records will be described at baseline by means of frequencies (percentages) or means (SD). Independent *t*-test for continuous data and chi-square test (*χ*^2^) for categorical data will be conducted to confirm that there were no demographic or clinical differences between groups at baseline. Following the CONSORT guidelines [38], Intention-To-Treat analysis will be performed using Maximum Likelihood estimation via Expectation Maximization imputation [67]. The procedure suggested by Hair et al [68] will be followed to handle missing data: 1) the types of missing data and percentage of missing will be analyzed to ensure that none exceed the recommended thresholds; 2) Little’s MCAR (Missing Completely At Random) test will be used to assess whether the missing data is completely random; and 3) sensitivity analysis will be performed to determine the impact of missing data on the results of a study, comparing the main outcomes between completers and imputed values.

*Multilevel Modelling (MLM)*. First, efficacy of MBHC and MBHC-VR compared to WL control condition will be analyzed by using MLM. Multilevel analysis enables the control of variance associated with random factors without the need for data aggregation. Variance across participants, instructor of each group, and subgroup of delivery (i.e., edition) will be modeled as random effects. Group (i.e., MBHC, MBHC-VR, and WL) and time (i.e., pre-intervention, inter-session, post-intervention, and 3-month follow-up) will be modeled as fixed effects. Analyses will be conducted via restricted maximum likelihood estimation (REML), which provides a less biased estimate of variance components with small sample sizes [69]. The group x time interaction will be used to study the trajectories of each group throughout the intervention and to determine whether the between-group differences are maintained over time.

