P-values will be obtained through likelihood ratio tests comparing the full model (including the effect in question) with the model that excludes this effect. Z-values will be obtained to test the significance for fixed effects (estimates and standard errors data in the tables). Trends of the longitudinal data will be studied by testing the linear trend of the model for all the outcomes. Interaction effects between time and predictors will be performed. To estimate the magnitude of between-group differences at post-intervention and 3-month follow-up, effect sizes (Cohen’s *d*) will be calculated by dividing the differences in means by the pooled standard deviation (SD). The Cohen convention was used to interpret effect sizes, where effect sizes of 0.20 are categorized as small, effect sizes of 0.50 are classified as medium, and effect sizes greater than or equal to 0.80 are considered large.

Model comparison approach will follow Bliese and Ployhart [70] and Bliese [71] guidelines. The process begins by examining the nature of the outcome. To test the significance of person effects, a likelihood ratio test will be conducted to compare the null multilevel model (i.e., unconditional model) with a null single-level model, testing the null hypothesis that there are no group differences. The second step involves estimating the intraclass correlation coefficient (ICC) to calculate the between/within variation ratio. Model fit will be assessed using chi-square tests on the log-likelihood values and the Akaike’s information criterion (AIC) [72] relative goodness of fit index. According to the change in these fit indexes, the model with the last significant change will be chosen for each analysis.

MLM will be performed using the lme4 R package [73]. P-values of the lme4 outputs will be obtained by the lmerTest R package [74]. The Intraclass Correlation Coefficient (ICC) will be calculated by the sjstats R package [75]. Graphic data processing will be performed by the ggplot2 R package [76]. Visual inspection of q-q plots by the car R package [77] will reveal any deviations from homoscedasticity or normality in the dependent variables. In order to calculate multiple comparisons, Tukey/Bonferroni correction tests will be performed.

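### No test is named as decisive for the treatment effect, and the rule for choosing the model does not protect the group x time term that carries it

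*Protocol article*

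**What the plan says.** All of this is in the protocol article. Its sample size section powers the group x time interaction, and its multilevel modelling paragraph uses that interaction to compare the arms' trajectories and to judge whether differences last. The Hypotheses section fixes the occasion: "All hypotheses will be tested in the post-training assessment, except for hypothesis 5".

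The quantitative data analysis plan then gives these rules for significance:

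- a model comparison for a whole effect: "P-values will be obtained through likelihood ratio tests comparing the full model (including the effect in question) with the model that excludes this effect";
- a second rule, given straight after it and applied to single coefficients: "Z-values will be obtained to test the significance for fixed effects";
- a third, in the software paragraph: "P-values of the lme4 outputs will be obtained by the lmerTest R package".

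Model fit is judged by chi-square tests on the log-likelihood and by AIC, and the selection rule is: "According to the change in these fit indexes, the model with the last significant change will be chosen for each analysis". Two further commitments matter here. Cohen's d will be calculated at post-intervention and follow-up, as a difference in means over the pooled SD. A Tukey/Bonferroni correction is planned for multiple comparisons, without saying which of the two applies or to what family of tests.

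**The concern.** Two things are left open.

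**Which test decides.** A likelihood ratio test of group x time asks one joint question. With three questionnaire occasions and three arms it has (3 - 1) x (3 - 1) = 4 degrees of freedom. A z-value or an lmerTest coefficient p-value asks about one programme at one occasion. The two can disagree, and no sentence says which verdict counts for a hypothesis.

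**Whether the treatment term stays.** Selection is made separately for each analysis and depends on significance. It is not limited to random effects or error structure, and group x time is not protected. If the interaction drops out, any group term left is a difference assumed equal at all occasions, baseline included. That does not address Hypotheses 1 to 4 at post-training.

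At stake are the error rate for each outcome, the size of the estimates that survive selection, and the value of a null result for VR against MBHC. A null is useful only with an interval showing how much benefit remains possible.

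**Working it through.** **1. The plan's own figure.** The plan states "With an alpha criterion of .05 and a small effect size" and "to achieve a minimum of 80% power, a minimum sample size of 174 participants will be needed". With 3 groups and 4 occasions, the interaction F test has df1 = 2 x 3 = 6 and df2 = 3 x (174 - 3) = 513. Reading .08 as f-squared, lambda = 0.08 x 174 = 13.92 and power is 0.804. The smallest N is 173, or 174 for three equal arms. So 174 reproduces as a test of group x time, with sphericity assumed. The powered term is the one that selection can remove.

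**2. Inputs for the check.**

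- Alpha: "statistical tests with a significance level of alpha < .05".
- Per arm: 210 x 0.8 / 3 = 56, the planned sample after the planned 20% dropout.
- Occasions: 3, because Table 1 collects the questionnaires at pre, post and follow-up only; the inter-session occasion is EMA.
- Assumed: correlation 0.5, balanced data, SD 1 at each occasion, ML fits for the likelihood ratio.
- Assumed effect: VR only, d = 0.28 at post and follow-up. This is the square root of .08, the literal reading of the stated d-squared. It is not the reading that reproduces 174.

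**3. Formulas.**

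- Likelihood ratio: reject if chi-square on 4 df exceeds 9.49.
- AIC: keep the term if that chi-square exceeds 2 x 4 = 8.
- z: each programme's change against WL at post and follow-up, four tests. Residual variance is 1 - 0.5 = 0.5, so SE = sqrt(4 x 0.5 / 56) = 0.189. The cutoff is 1.96, or 2.50 with Bonferroni (.05/4, two-sided).

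**4. No true effect (20,000 simulated trials, per outcome).**

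| Rule | False positives |
|---|---|
| Likelihood ratio | 5.3% |
| AIC alone | 9.7% |
| Any of four z, uncorrected | 16.6% |
| Likelihood ratio or any z, uncorrected | 17.5% |
| Any of four z, Bonferroni | 4.6% |
| Likelihood ratio or any z, Bonferroni | 7.1% |
| Likelihood ratio, AIC or any z, Bonferroni | 10.4% |

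The likelihood ratio and z verdicts conflict in 13.1% of trials without correction and 4.3% with Bonferroni. A repeat run agreed within about 0.6 percentage points throughout.

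**5. Only VR effective, d = 0.28.** The interaction sum of squares per participant is 0.28² x 2/3 x 2/3 = 0.0348, so the noncentrality is 56 x 0.0348 / 0.5 = 3.90. The chance that a chi-square on 4 df with that noncentrality exceeds 9.49 is 31%; simulation gives 32%. Among trials that keep the term, the mean VR-versus-MBHC estimate at post-training is 0.415, and 0.415 / 0.28 = 1.48.

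**6. Can AIC loosen a chi-square rule?** The .05 cutoffs are 3.84, 5.99, 9.49 and 12.59 at 1, 2, 4 and 6 df, against AIC thresholds of 2, 4, 8 and 12. A significant chi-square therefore always lowers AIC too. AIC adds false positives only if it may decide alone; its implied alpha is then 15.7%, 13.5%, 9.2% and 6.2% at those df.

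**The case against.** The strongest case is that the rules complement each other: the likelihood ratio for a whole effect, z-values as table output, and lmerTest as the software source. An omnibus test followed by coefficients is routine, and the likelihood ratio and lmerTest joint tests nearly coincide at this sample size. The selection sentence also closes a paragraph about the null model, the ICC and fit, so it may concern random structure only. This is a plausible account of intent. But the text never says it, and choosing a model for each analysis reads as general.

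A reader might infer three stronger things that the document does not support.

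- **That the false-positive rate is well above .05.** That needs an analyst who claims whichever rule passes, and the 17% figure also needs uncorrected z-values. The planned Tukey/Bonferroni correction could bring it to about 7%.
- **That AIC by itself loosens the rule.** The sentence asks for a significant change, which most naturally means chi-square at .05, and step 6 of the working shows AIC then adds nothing.
- **That estimates will exist only for outcomes that passed.** Cohen's d at post-intervention and follow-up is promised whatever model is chosen. It is defined from means and a pooled SD, with no stated interval and no link to the model, so it only partly replaces a model contrast.

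The two harms also come from different readings and should not be added together. The 48% exaggeration uses the strict chi-square filter. If AIC decided instead, the term would be kept in roughly 42 to 43% of trials, with a mean of 0.39.

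**Conclusion.** The point holds in a conditional form. The plan names no decisive test, and its stated selection rule can remove the term that carries the treatment comparison. This is a rule written down without a needed exemption, not detail left to another document.

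The sizes are per outcome and rest on balanced data, 56 per arm, three occasions and correlation 0.5. With d = 0.28 for VR only, a .05 filter keeps group x time in 32% of trials, with estimates about 48% too large on average there. If any rule may decide, the null rate is about 17% uncorrected and about 7% with Bonferroni over four z-tests; letting AIC decide alone as well raises the latter to about 10%. If the authors intend one joint test, with selection limited to random structure, the rate is about 5% and nothing is lost, but the article needs to say so. The change should be made; it does not call the design into question.

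**What to change.** State in the analysis plan:

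1. For every outcome, fit one fixed model with group, time as categories and group x time, all kept whatever their p-values.
2. Decide each hypothesis by one named model contrast at its stated occasion (post-training, or follow-up for Hypothesis 5), using lmerTest degrees of freedom and the planned multiplicity correction, with its type and family named.
3. Report that contrast with a 95% CI whether or not it is significant.
4. Confine AIC and likelihood ratio selection to the random-effects and residual structure.
5. Coefficient z-values may stay in the tables as description, but decide no hypothesis.

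The cost is wording only. No participants or data are added, and there is less modelling to do. The downside is that non-significant terms stay in the tables.

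### Single-step Tukey/Bonferroni correction of the three arm contrasts gives up power that a closed step-down test would keep at the same 5% familywise rate; for MBHC-VR versus MBHC the loss is up to about 12-15 points

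*Protocol article*

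**What the plan says.** All of this is in the protocol article.

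- **Quantitative data analysis plan.** The multilevel model has a three-level arm factor: "Group (i.e., MBHC, MBHC-VR, and WL"), crossed with time. The level is set by "statistical tests with a significance level of alpha < .05". Multiplicity gets one sentence: "In order to calculate multiple comparisons, Tukey/Bonferroni correction tests will be performed". It does not say which of the two methods applies, or whether the family is arms, time points or outcomes. No step-down or closed procedure is named.
- **Hypotheses.** Hypotheses 1 to 3 compare each programme with the waiting list (WL), for example "both MBHC and MBHC-VR will improve occupational indicators (Hypothesis 1"). Hypothesis 4 expects MBHC-VR to do better than MBHC. All are tested at post-training except Hypothesis 5, which is tested at follow-up. The introduction makes MBHC without versus with VR the main objective.
- **Sample size estimation.** The reference effect is "a small difference in perceived stress between MBHC with vs without VR-assisted meditation in university students", entered as a "small effect size (Cohen’s d^2^ = .08"). The group-by-time interaction is powered for Hypotheses 1, 2, 3 and 5. Hypothesis 4 is not listed.

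**The concern.** Three arms give three pairwise null hypotheses, and these are logically linked. If one is false, the other two cannot both be true. Once the largest contrast has passed a familywise limit, at most one true null remains, so each remaining contrast can be tested at the full .05 without exceeding 5% overall. Single-step Tukey or Bonferroni ignores this and holds every contrast to the stricter limit.

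The smallest contrast pays most. The plan expects the VR difference to be small, while its introduction reports small-to-moderate effects of mindfulness programmes against passive controls. MBHC-VR versus MBHC is thus likely to be the contrast that falls between the two limits, and it is the main objective, with no stated power of its own.

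**Working it through.** **1. The plan's own sample size.** For a within-between interaction with k = 3 arms and m = 4 times, the noncentrality is λ = f²·N·m/(1 − ρ), on (k − 1)(m − 1) = 6 and (N − k)(m − 1) degrees of freedom. With d² = .08, d = √.08 = 0.283 and f = d/2 = 0.141. At ρ = 0 and N = 174, λ = 0.02 × 174 × 4 = 13.92 on 6 and 513 df, and power is 80.4%. This reproduces "to achieve a minimum of 80% power, a minimum sample size of 174 participants will be needed". The pair f = 0.10, ρ = 0.5 also gives 174. With f = 0.141 and ρ = 0.5 the answer would be 90, so the correlation of 0.5 used below is my assumption and not an input that yields the plan's figure.

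**2. Inputs for the pairwise contrast.**

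| Input | Value | Source |
|---|---|---|
| Alpha | .05, two-sided | stated; sidedness assumed |
| VR minus MBHC | 0.283 SD | stated d² |
| Completers per arm | 70 × 0.8 = 56 | stated 70 per arm, 20% dropout |
| Baseline correlation r | 0.5 | assumed |
| MBHC minus WL | 0 to 0.5 SD | assumed |

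**3. Critical values and power by single-step methods.** With 3 × 56 − 3 = 165 df, the limits for |t| are 2.419 (Bonferroni), 2.365 (Tukey) and 1.974 (unadjusted). The standard error of a baseline-adjusted contrast is √[(1 − r²)·2/n] = √(0.75 × 2/56) = 0.164 SD, so the noncentrality is 0.283/0.164 = 1.73. Noncentral-t power is 24.8% for Bonferroni and 26.5% for Tukey. The unadjusted test gives 40.5%, which is the ceiling for any step-down test.

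**4. Power of the Tukey-first step-down test** (simulation of three arm means, same inputs):

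| MBHC minus WL (SD) | Tukey | Step-down Tukey | Plain Holm |
|---|---|---|---|
| 0 | 26% | 31% | 27% |
| 0.2 | 26% | 38% | 30% |
| 0.4 | 26% | 40% | 35% |
| 0.5 | 26% | 40% | 38% |

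The gain over Tukey runs from about 5 points when MBHC equals WL to about 14 points at 0.4 SD. Holm gains less because it ignores the logical link between the three hypotheses.

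**5. Other inputs at d = 0.283** (ceiling = unadjusted test):

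| n per arm | r | Bonferroni | Tukey | Ceiling |
|---|---|---|---|---|
| 56 | 0 | 18.1% | 19.6% | 31.9% |
| 70 | 0 | 23.2% | 24.8% | 38.4% |
| 70 | 0.5 | 31.7% | 33.6% | 48.5% |

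So 18-34% rises to at most 32-49%. The largest possible gain over Tukey is 12 points (31.9 − 19.6) to 15 points (48.5 − 33.6). At d = 0.2, 9-16% rises to at most 18-28%.

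**6. Error rates, one outcome and one time point, n = 56.** Under the global null, Tukey and step-down Tukey share the same first step and both give 5.0-5.1%, which is 5% within simulation error. If VR equals MBHC and both beat WL by 0.2, 0.5 or 0.8 SD, the false-positive rate for the VR pair is 1.6-1.9% single-step. Step-down Tukey gives 3.4%, 4.9% and 5.0%.

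**7. Two time points tested separately** (correlation 0.5 assumed). Under the global null both methods give about 9.1%. If VR equals MBHC and WL clearly differs, the chance of at least one false VR claim is 3.6% with Tukey and 9.0% with step-down.

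**The case against.** Tukey and Bonferroni are valid, standard corrections, and a condensed sentence in an article may be sharpened in an analysis plan that is not shown. That is fair. A reader might infer that the plan's correction is an error or inflates the type I error; it is not and does not. The point is only that the method named is less efficient than one that costs little.

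The family is undefined. If it spans time contrasts or outcomes, the limits of 2.37 to 2.42 and the three-hypothesis argument do not describe the plan. The plan also tests effects by likelihood ratio and z-values, so it is not certain that Hypothesis 4 will be judged by the corrected pairwise test. This stands, and the conclusion is conditional on the three-contrast family.

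A reader might also infer that the gain is free. It is not. It comes from using alpha that single-step tests leave unspent, and simultaneous confidence intervals that match the tests exactly are lost. With six main outcomes at one time point, n = 56, VR equal to MBHC and both 0.4-0.5 SD better than WL, the chance of at least one false VR claim rises from about 7-11% to 16-26%, for assumed between-outcome correlations of 0.7 down to 0. Against that, the plan promises no simultaneous intervals, and its single-step correction carries no stated control across outcomes or time points either.

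Finally, the calculation uses independent arm means with equal residual variance, whereas the plan models instructor and edition as random effects. The power figures illustrate the size of the gain; they do not predict the planned model's power.

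**Conclusion.** The concern holds in a conditional form. If the family is the three arm contrasts within one outcome and time point, a Tukey-first closed step-down test keeps the familywise rate at 5% and rejects everything single-step Tukey rejects, sometimes more. The result of 25-27% rising to about 40% is a worked example and not a property of the trial: it needs the inputs in step 2 and a clear programme effect against WL.

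It would be tempting to conclude that the change rescues Hypothesis 4. It does not. Even the best case examined with r up to 0.5 is 49%, and the sample size section does not power that hypothesis. This is a worthwhile, inexpensive improvement, separate from the question of sample size.

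**What to change.** Replace the multiplicity sentence with text to this effect: within each outcome, the three pairwise arm contrasts at post-intervention are tested step-down; the largest must pass the Tukey limit at .05, and only then are the other two each tested at .05; otherwise none is declared. The same procedure is applied separately at follow-up. Familywise control is per outcome and per time point, and no control across outcomes or time points is claimed.

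Name the procedure as a closed test with Shaffer or Westfall adjustment (both are options in the R package multcomp), not plain Holm. The Westfall version matches the Tukey first step. Report Tukey or unadjusted 95% intervals beside the adjusted p-values, and say that they do not correspond exactly to the tests.

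The cost is a few lines of text and one software option, with no extra participants. The change should be made before the outcome data are analysed by arm.

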The main objective of this study is to examine the differential effects of a Mindfulness-Based Health Care Program (MBHC) without versus with VR-assisted meditation (MBHC-VR) on OB and mental health (i.e. psychological distress) in university students. Our seven objectives are:

To compare the training effects on occupational indicators, such as occupational balance, eating habits, sleep and physical activity.To compare the training effects on mental health indicators, such as anxiety, depression, stress and burnout.To compare the training effects on psychological functioning, such as emotional regulation, acceptance, mindfulness-trait, self-compassion and life satisfaction.To test whether the training effects are maintained 3 months post-completion of MBHC.To identify potential mechanisms of change in MBHC vs MBHC-VR.To examine expectations of the participants before their participation in the program.To qualitatively explore the perceptions of the participants about the program and its effects after its completion.

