#### Waiting list control group (WL)

Participants in the WL control group will not receive any intervention during the study. However, for ethical reasons, at the end of the 3-month follow-up assessment, participants of this WL control group will be invited to participate in the MBHC program free of charge.

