*Structural equation model (SEM)*. We will use the lavaan R package to implement structural equation models (SEM) by to investigate whether there are any significant mediators of training outcome. Results will be reported following the recommendations in Raykov et al. [78]. Cases with missing values and outliers will be detected using Mahalanobis distance. Multivariate and univariate normality assumptions will be tested using Mardia’s test and Kolmogorov-Smirnov’s test with the MVN R package [79]. If non-normality is found, Satorra-Bentler scale test and standard bootstrapping will be used. Model fit will be assessed using several criteria [80]: 1) a ratio of *χ*^2^*/gl<2* suggests an acceptable fit; 2) A RMSEA size below .06 suggests a well-fitting model; 3) a comparative fit index (CFI) above .95 indicates a good fit; 4) a SRMR of less than .09 also indicates a good fit; and 5) The chi-square statistic provides a conventional measure of model fit.

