In this study, special attention is also paid to the possibility of adverse effects associated with the practice of meditation, as evidenced by previous studies [64, 88, 89]. In anticipation of this, the participants will communicate to the research team any difficulty or symptomatology that may arise, in order to attend to and solve these events as quickly as possible and, if necessary, refer the participant to the specialized psychological services available at the university. Likewise, participants will also report possible adverse effects during and/or after VR exposure. In the MBHC-VR group of this research, VR with neutral and pleasant contents will be used in all sessions for a time between 10 and 15 minutes, favoring adaptation to the exposure and minimizing possible adverse effects.

It is also worth mentioning that the programs will be implemented by a multidisciplinary professional group with extensive experience in university education and highly qualified in MBIs. In this sense, the team is made up of occupational therapists, psychologists, physiotherapists, mindfulness experts and university professors’ experts in teaching and research.

In terms of feasibility, face-to-face interventions will be carried out in groups of about 15 people, who can be attended simultaneously, thus being a low-cost community mindfulness program for university students. If the MBHC programs designed for this study are effective, one of the advantages is that their applicability can be extended to other universities. Also, the materials and procedures will be available to the educational and scientific community. Thus, the range of effective interventions available to address university students’ mental health will be expanded.

The present trial can also contribute to expanding knowledge on personalized treatments. Baseline characteristics of individuals have started to be used as predictive factors of differential response to intervention strategies. This study will allow identifying individuals within the included sample that will benefit more from utilizing one condition relative to the other. It will also allow to establish moderating mechanisms of efficacy.

In short, and from the point of view of clinical practice, it is expected that with the proposed intervention university students will learn to relate in a healthier way with their mental processes, so as to improve their OB and their psychological well-being.

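### The mediation SEM for Hypothesis 6 makes no provision for the instructor and delivery-group clustering that the multilevel model includes, so its arm-to-mediator standard errors are too small if classes differ

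*Protocol article*

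**What the plan says.** All places are in the protocol article.

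- **Quantitative data analysis plan, multilevel modelling:** "Variance across participants, instructor of each group, and subgroup of delivery (i.e., edition) will be modeled as random effects".
- **Same section, structural equation model:** "We will use the lavaan R package to implement structural equation models (SEM"), with the purpose of finding mediators of training outcome. The paragraph goes on to outlier detection, normality tests and five fit criteria. On inference it adds: "If non-normality is found, Satorra-Bentler scale test and standard bootstrapping will be used". It mentions no class, edition or instructor.
- **Hypotheses (Hypothesis 6):** "psychological functioning variables will act as mechanisms of change of occupational balance and mental health indicators in experimental vs control condition".
- **Introduction (list of objectives):** "To identify potential mechanisms of change in MBHC vs MBHC-VR".
- **Discussion:** "face-to-face interventions will be carried out in groups of about 15 people".
- **Waiting list control group:** "Participants in the WL control group will not receive any intervention during the study".
- **Test level:** "statistical tests with a significance level of alpha < .05".

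**The concern.** The plan accepts in one model that students taught together may resemble each other, then analyses the same students in a second model without that allowance. The two stated remedies do not fill the gap. The Satorra-Bentler correction deals with non-normality. Standard bootstrapping, as ordinarily understood, resamples students one at a time.

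The direction matters. Only the programme arms are taught in classes, and class effects arise after randomisation. A difference between classes in, say, mindfulness or self-compassion therefore enters the arm-to-mediator path directly and widens its true sampling variance. A model that ignores this reports too small a standard error, and a chance difference between a few classes can pass as a mechanism of change. Correcting the multilevel model does not help, because the SEM has its own standard errors.

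**Working it through.** **Figure in the plan.** The protocol gives no ICC and no error rate for the SEM beyond the nominal 5%, so there is nothing to reproduce. The test is taken as two-sided.

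**Inputs**
- From the protocol: 70 per arm, about 20% dropout, classes of about 15, WL untaught.
- Analysed per arm: 70 × 0.8 = 56, taken as 4 classes of m = 14.
- Assumed: ICC of the mediator .02 to .10, class effect nested in arm, mediator-outcome correlation .5, no programme effect on the mediator.

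**Step 1: arm-to-mediator path by formula.** The design effect is D = 1 + (m − 1) × ICC. The ratio v of true to assumed variance of the arm contrast is:
- MBHC-VR versus MBHC (both arms clustered): v = D
- one programme versus WL: v = (D + 1)/2
- both programmes pooled versus WL: v = (D/2 + 1)/1.5

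The rejection rate at nominal 5% is 2 × [1 − Φ(1.96/√v)].

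Example at ICC .05: D = 1 + 13 × .05 = 1.65. One programme versus WL: v = 2.65/2 = 1.325, and 1.96/√1.325 = 1.70, so the rate is 8.9%.

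| ICC | D | Pooled vs WL | One programme vs WL | MBHC-VR vs MBHC |
|---|---|---|---|---|
| .01 | 1.13 | 5.5% | 5.8% | 6.5% |
| .02 | 1.26 | 6.0% | 6.5% | 8.1% |
| .05 | 1.65 | 7.6% | 8.9% | 12.7% |
| .10 | 2.30 | 10.2% | 12.7% | 19.6% |

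**Step 2: indirect effect by simulation.** Null trials (4,000 per setting) with the inputs above, clustering ignored, and a Monte Carlo interval for the indirect effect:

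| ICC | Pooled vs WL | One programme vs WL | MBHC-VR vs MBHC |
|---|---|---|---|
| .02 | 5.8% | 7.2% | 9.0% |
| .05 | 7.2% | 9.3% | 13.0% |
| .10 | 9.8% | 13.0% | 19.7% |

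A separate simulation gave 5.7/8.0/10.0%, 7.0/9.2/13.1% and 9.1/13.9/20.3% for the three columns. At zero ICC the rate is about 5-6%.

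**Step 3: the bootstrap branch.** Here a percentile bootstrap resampled individuals, with 58 per arm (174/3), classes of 15 and ICC .05. With a mediator-outcome coefficient of .3 or .5 it rejected in 8.9% and 11.4% of trials for one programme versus WL, and in 12.4% and 13.5% for MBHC-VR versus MBHC. With a coefficient of 0 it rejected in under 1%.

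**Step 4: the remedy.** A class-level arm contrast with Satterthwaite degrees of freedom (20,000 null trials) gave 5.2-5.4% (pooled versus WL), 5.5-6.1% (one programme versus WL) and 3.9-4.1% (MBHC-VR versus MBHC). A plain cluster-robust error with normal critical values still gave 8.8-10.6% (one programme versus WL) and 11.4-12.3% (MBHC-VR versus MBHC).

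**The case against.** **Silence is not a choice.** A reader might infer that the protocol specifies a single-level SEM. It does not: that term appears only for a null-model comparison in the multilevel section, and lavaan can handle clusters. An article may also leave detail to a fuller plan. This stands against the label. It does not remove the point, because the paragraph is specific about package, normality remedy and fit criteria, and allows for clustering in neither branch.

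**The bootstrap is conditional.** A reader might take standard bootstrapping as the planned method throughout. It applies only if non-normality is found. This stands.

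**A general error rate cannot be stated.** A reader might infer that mechanisms will be found by chance at some fixed inflated rate. The ICC is undocumented, and the rates need a mediator that relates to the outcome and is not moved by the programme. That is still the relevant null: Hypothesis 6 presupposes the relation, and both variables are self-reports from the same visits.

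**The clustering structure is not settled.** Two instructors conduct both programmes, so instructor may be crossed with arm. If edition means a calendar wave containing all three arms, ignoring it is slightly conservative: 2 × [1 − Φ(1.96/√(1 − ICC))] gives 4.4% at ICC .05 and 3.9% at .10. The inflation needs a class effect nested in arm. Separate in-person classes of about 15 for each programme make that plausible, but the document does not state it.

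**Other evidence exists.** A reader might infer that the mechanisms objective rests on the SEM alone. The Introduction also assigns exploration of mechanisms to focus groups, and the proposed mediators are secondary outcomes analysed in the multilevel model. This softens the consequence. It does not correct the test of the indirect effect.

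**Conclusion.** The point holds as an inconsistency within the plan: clustering is modelled for efficacy and left out of the only quantitative test of Hypothesis 6. Followed as written, the SEM understates the arm-to-mediator standard error if classes within an arm differ.

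Under the assumptions listed in the working, the ranges are 6-10% for the pooled programmes and 7-13% for one programme against WL, which are the contrasts Hypothesis 6 could mean. The largest range, 9-20%, is for MBHC-VR versus MBHC, the contrast named in the mechanisms objective, because both of its arms are taught in classes. The upper ends need an ICC of .10. The defect does not touch the efficacy tests and can be corrected before analysis.

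**What to change.** State in the SEM paragraph that inference on mediated effects accounts for delivery class. One workable form:

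- Take the arm-to-mediator path from the mixed model already planned, with a random class effect in the programme arms only (each WL student a class of one) and Satterthwaite degrees of freedom from lmerTest, which the plan already uses.
- Combine that path with the mediator-to-outcome path by a Monte Carlo interval.
- Keep the lavaan SEM and its fit criteria for model structure and fit.
- Say whether edition means a class within one arm or a calendar wave across arms.

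Adding only a cluster-robust error with normal critical values is not enough with four to eight classes.

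The cost is wording, a few lines of R and wider intervals for mediated effects. The widening is greatest for MBHC-VR versus MBHC: 4 + 4 − 2 = 6 degrees of freedom remain, the critical value rises from 1.96 to about 2.45, and the test becomes slightly conservative.
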